### Secondary endpoints

Number of seroma aspiration-punctures requiredPain (measured by visual analogue scale, VAS)Axillary seroma volume (measured by axillary ultrasound in cm.^3^)Number of post-operative emergency room visitsNeed for hospital readmissionPresence of lymphoedema in the armQoL after the intervention (measured by the EQ-5D-5L questionnaire, Spanish version)

### Main safety measures

The main safety measures are as follows: adverse events and post-surgical complications such as suture failure and surgical wound infection.

### Other study variables

Surgical wound infection: defined as the presence of inflammatory signs—heat, redness, increased temperature and/or pain—requiring antibiotic treatment with or without surgical or percutaneous drainageSurgical regimen: major outpatient surgery [11] or short-stay hospitalization (first 24–48 h post-operatively)Anesthetic technique performed. Use of neuromuscular blockade prior to surgeryDefinitive pathological anatomy (number of axillary lymph nodes)

### Participant timeline {13}

After surgery, all patients in the study will follow the same clinical assessments, which will be at days 7, 14, and 30 post-surgery. Patients will also be evaluated in the long term, at 6 and 12 months after surgery (Table 1). Clinical visits outside those that are established will be made at the discretion of the surgeon at each participating center.

**Table 1 Tab1:**
[figure not shown]
Schedule of enrolment, interventions, and assessments

During clinical assessments, data on the level of pain (VAS), adherence to prescribed analgesic medication, presence of symptomatic seroma, need for puncture-evacuation of the seroma, and QoL will be collected.

### Sample size {14}

Accepting an alpha risk of 0.05 and a beta risk of 0.2 in a bilateral contrast, 67 subjects in each study arm are required to detect a statistically significant difference in the percentage of patients with symptomatic seroma (which is expected to be 25% for the control group and 7% for the study group). A loss to follow-up rate of 10% has been estimated.

For the calculation of “*n*” and due to the large extent of seroma described in the literature, reference values of 25% described in the study by Jan et al. [9] have been taken.

### Recruitment {15}

All the hospitals participating in this trial have a breast cancer unit, all of them treating more than 100 BC patients a year. Hospitals without a breast cancer unit are not included.

The recruitment of patients must end by December 2024. For this reason, the hospitals included in the trial can be expanded during 2023 with the objective to include the required number of centers in each arm. The minimum number of patients required in each hospital is 5, and the maximum is 10.

The main investigator from each hospital is responsible for identifying potential patients who meet the study inclusion criteria. If there is any patient who required a conservative treatment in the breast and a lymphadenectomy, the main investigator must inform the patient about the trial.

## Assignment of interventions: allocation

### Sequence generation {16a}

The allocation of participants to the different groups has been carried by means of a computer-generated randomization stratified by center.

### Concealment mechanism {16b}

Randomization lists have been prepared using the REDCap (Research Electronic Data Capture) program. At the time of recruitment, each participant is assigned a personal and non-transferable study identification number.

REDCap is a secure and customizable web-based database application used to collect and store research data from case report forms, surveys, or a combination of both.

### Implementation {16c}

The surgeon will enter the affiliation data of the patient within the REDCap program. If the inclusion criteria in the trial are met, the program will randomize the patient. The surgeon will be the only person that knows the group in which the patient is allocated. The main investigator of each hospital will be able to review what arm each patient has been assigned to.

## Assignment of interventions: blinding

### Who will be blinded {17a}

Patients, trial statisticians, and postoperative care nurses will be blinded after assigning the intervention.

### Procedure for unblinding if needed {17b}

In case of withdrawal from the trial, the patient will be able to know in with arm of treatment was allocated.

## Data collection and management

### Plans for assessment and collection of outcomes {18a}

For each patient included in the study, a patient case report form (CRF) will be filled in. This also applies to patients who do not complete the full follow-up foreseen in the trial. Subjects will not be identified by name or initials in the CRF or in any trial document. The only acceptable identification that will appear on the CRF or other documents is the subject’s unique subject identification number. The investigator will retain the contact details of all participants, so that they can be contacted quickly if necessary.

Data will be collected via a study-specific electronic case report form (eCRF) by using REDCap program. This eCRF include the necessary fields to fill in during every visit (7, 14, and 30 days and 6 and 12 months). Final data will be cheeked by an independent data monitoring committee which will verify the veracity of the data and the absence of duplications. The database will only be locked for the final analysis, after all data management and statistical data validation checks have been satisfactorily resolved.

QoL will be measured by EQ-5D-5L questionnaire (Spanish version) [12]. This questionnaire has been validated by EuroQol in 2009. EQ-5D-5L measures mobility, self-care, usual activities, pain/discomfort, and anxiety/depression, with four levels of severity in each dimension: no problem, some problems, serious problems, or disability.

Pain is measured by the visual analogue scale (VAS), ranging from 0 to 10.

The REDCap program makes it easy to fill in the patient data without errors in measurements, since if they are not correct, it does not allow them to be recorded.

Data in the eCRF will be checked by the main investigator before the extraction. Data also will be extracted by the statisticians and double checked to avoid duplication or typographical errors.

### Plans to promote participant retention and complete follow-up {18b}

The nurses of each breast cancer unit will be the ones checking that the patients have the appointments established according to the trial.

### Data management {19}

Data registered in the eCRF will be filled in by the surgeon in charge of each patient. An independent data monitoring committee will, at the end, check all data to make sure there are no duplications or other errors. The main investigator of the trial will also validate data periodically. Data discrepancies will be flagged to the study site, and any data changes will be recorded to maintain a complete audit trail (reason for change, date when the change was made, and who made change).

### Confidentiality {27}

The patient’s clinical data shall be completely dissociated from any information that would allow identification of the patient. In all reports and communications relating to trial subjects, the subject will be identified only by case number. The main investigator of each hospital (surgeon) will be the one to register all data in the eCRF; besides him, no one else will have access to it. All data will be registered in fields in REDCap program with a single password, so that no one apart from main investigator can open it.

This file will be treated strictly according to professional standards of confidentiality and will be archived under appropriate security measures and restricted access, in the terms provided for in Regulation [11] 2016/679 of the European Parliament and of the Council of 27 April 2016 on Data Protection (RGPD) as well as in the Organic Law 03/2018, of 5 December.

### Plans for collection, laboratory evaluation, and storage of biological specimens for genetic or molecular analysis in this trial/future use {33}

This trial does not include biological specimens.

## Statistical methods

### Statistical methods for primary and secondary outcomes {20a}

The statistical analysis plan (SAP) will be based on intention to treat principles in line with Consolidated Standards of Reporting Trials (CONSORT) guidelines.

Descriptive analysis of the study sample is as follows: as quantitative variables, the mean, median, range, and standard deviation will be analyzed. Absolute values and percentages will be used for qualitative variables. The frequency measures used will be prevalence, analysis of the homogeneity, or comparability of study groups. Quantitative variables will be assessed for normal distribution using the Kolmogorov–Smirnov or Shapiro–Wilk test.

Bivariate analysis of quantitative variables will be performed using Student’s *t*-test or Mann Whitney *U* test as appropriate.

For the analysis of qualitative variables, the chi square test or Fisher’s test will be used as appropriate. The OR (odds ratio) is considered as a measure of effect calculated by logistic regression.

In the multivariate survival analysis, the Cox regression method will be used, while for the multivariate analysis of risk factors, the logistic regression method will be used, introducing in the statistical model those variables that show statistical significance in the univariate analysis and/or those that in the bibliography and theoretical framework are prognostic factors.

Clinical lymphoedema-free survival will be analyzed using the Kaplan–Meier method, and survival curves will be compared using the Long-Range test and Cox regression. The safety analysis will be performed per protocol and will use the same statistical tests mentioned above. The level of significance is set at *p* < 0.05. The statistical analysis will be carried out with the Statistical Package for the Social Sciences (SPSS) version 21.

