**Methods:**

This is a prospective, multicenter, international, and randomized clinical trial. Patients undergoing conservative surgery and axillary lymphadenectomy for breast cancer will be randomized to control group (lymphadenectomy without sealant) or interventional group (lymphadenectomy with sealant Glubran 2®). In any of the study groups, drains are placed. Patients who received neoadjuvant treatment are included. Measurements of the study outcomes will take place at baseline; at 7, 14, and 30 days post-surgery; and at 6–12 months. The primary outcome is symptomatic seroma. Secondary outcomes are seroma volume, morbidity, quality of life, and lymphedema.

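### Randomisation is stratified by centre, but every arm comparison named in the analysis section ignores centre; if centre predicts outcome, the primary test is conservative

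*Protocol article*

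**What the plan says.** Under Sequence generation {16a}, allocation is a "computer-generated randomization stratified by center". Recruitment {15} sets a minimum of 5 and a maximum of 10 patients per hospital.

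Statistical methods for primary and secondary outcomes {20a} then names the tests. For categorical outcomes, which include the primary outcome, it reads "For the analysis of qualitative variables, the chi square test or Fisher". For continuous outcomes it reads "Bivariate analysis of quantitative variables will be performed using Student", with Mann-Whitney as the alternative. The odds ratio is to come from logistic regression, with no covariates named. The multivariable logistic model is for risk factors. Its covariates are chosen by univariate significance or from the literature, and centre is not mentioned. Centre is also absent from the subgroup variables in {20b}.

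On baseline values, the abstract says "Measurements of the study outcomes will take place at baseline", and Trial design {8} says that baseline data precede randomisation without naming the variables. Plans for assessment and collection of outcomes {18a} lists eCRF visits at 7, 14 and 30 days and at 6 and 12 months only.

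**The concern.** Stratified allocation removes between-centre variation from the treatment contrast. A test that ignores centre still counts that variation as noise. If centre is prognostic, the standard error is then too large and the p-value too cautious.

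The article gives reasons why centre might matter. Incision, closure and sealing device can vary (Intervention description {11a}). Inpatient or outpatient care is set by each hospital. Extra visits are at the surgeon's discretion. The primary outcome is itself a decision to puncture, so local thresholds could move the event rate.

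A second, smaller issue concerns pain (VAS) and EQ-5D-5L. If a pre-randomisation value exists, a two-sample test on follow-up values leaves precision unused.

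At stake is efficiency in a trial of about 134 patients whose planned power is 80%. The chance of a false positive result is not at stake.

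**Working it through.** **1. The plan's own figure.** Sample size {14} gives "Accepting an alpha risk of 0.05 and a beta risk of 0.2 in a bilateral contrast", rates "which is expected to be 25% for the control group and 7% for the study group", "67 subjects in each study arm are required to detect a statistically significant difference", and "A loss to follow-up rate of 10% has been estimated". The arcsine formula gives

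h = 2·asin(√0.25) − 2·asin(√0.07) = 1.047 − 0.535 = 0.512

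n = 2·((1.960 + 0.842)/h)² = 59.96, so 60 per arm; 60/0.9 = 66.7, so 67.

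The stated 67 is reproduced if it already includes the 10% loss. The article does not name its formula. The unpooled, pooled and continuity-corrected variants give 69, 72 and 84 with loss.

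**2. Number of strata.** 2 × 67 = 134 patients; 134/10 ≈ 13 and 134/5 ≈ 27 centres.

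**3. Unstratified chi-square against CMH by centre, no loss.** Simulations of 20,000 trials per setting used normal centre effects on the logit scale, exact balance within centre, and 13 centres of 10, 17 of 8 or 22 of 6. Marginal rates were 25% vs 7% for power and 16% in both arms for type I error. The centre SD is an assumption, since the documents give none. Latent ICC = SD²/(SD² + π²/3).

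| Centre SD (ICC) | Power, chi-square | Power, CMH | Type I error, chi-square |
|---|---|---|---|
| 0 (0) | 82.1-84.3% | 82.5-84.4% | 4.5-4.7% |
| 0.5 (0.07) | 83.3-84.3% | 84.1-85.1% | 4.1-4.7% |
| 1.0 (0.23) | 83.5-85.0% | 85.9-87.2% | 3.5-3.7% |
| 1.5 (0.41) | 84.1-85.9% | 88.7-90.3% | 2.7-2.9% |

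CMH holds its type I error at 4.5-5.0% throughout. Under the null, the unstratified standard error is too large by about 0-2%, 5% and 11-12% at SD 0.5, 1.0 and 1.5. For example, with 13 centres of 10 at SD 1.5, 0.0629/0.0565 = 1.11.

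**4. The same comparison with the protocol's 10% loss.** Centres of 5 and 7 were added, balanced as closely as their size allows before random loss. Each cell shows chi-square power, CMH power and the change.

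| Centres | SD 0 | SD 0.5 | SD 1.0 |
|---|---|---|---|
| 13 of 10 | 78.6 / 77.6 (−1.0) | 79.5 / 79.4 (−0.1) | 79.4 / 81.6 (+2.2) |
| 19 of 7 | 79.5 / 77.7 (−1.8) | 79.7 / 78.6 (−1.1) | 79.7 / 81.0 (+1.3) |
| 27 of 5 | 80.1 / 76.6 (−3.5) | 80.1 / 77.9 (−2.2) | 81.0 / 81.3 (+0.3) |

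At SD 1.5 the CMH gain is about 3-5 points. With centres of 5, about 46-52% of strata carry no information for CMH.

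Allowing for loss and small centres, the chi-square type I error is about 4.1-4.9% at SD 0.5, 3.7-4.1% at SD 1.0 and 2.9-3.4% at SD 1.5.

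**5. Baseline adjustment.** The variance factor is 1 − r². For assumed r = 0.3 it is 0.91 (9% lower); for r = 0.6 it is 0.64 (36% lower). If an unadjusted comparison has 80% power, the adjusted power is Φ(2.802/√(1 − r²) − 1.96): 83.6% at r = 0.3 and 89.9% at r = 0.5.

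**The case against.** Four objections have force.

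**Loss of power in general.** A reader might infer that the planned test loses power and that CMH is free of cost. The results with 10% loss do not support this. CMH is worse than chi-square at SD 0 in every layout, is no better at SD 0.5, and pays off clearly only when centres differ a good deal. The documents supply no centre SD. This objection stands, and it is why CMH is not put forward as the primary test.

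**Invalid p-values.** A reader might infer that the standard errors are wrong in a way that threatens the conclusion. Any error is on the safe side. It also requires balance within centre, and the article does not describe the blocks. With simple allocation, the chi-square type I error is about 5%.

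**Centre not shown to matter.** The Discussion says axillary lymphadenectomy should not differ between hospitals and calls the inpatient/outpatient regime irrelevant to the results. The sealant is to be applied uniformly after training. A centre effect is therefore plausible but not established.

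**Baseline values.** A reader might infer that baseline is ignored for all outcomes, or that two-sample tests at each visit are specified. The primary outcome, puncture count, seroma volume, emergency visits and readmission have no meaningful baseline value, and {20a} does not mention visit-by-visit testing. Only the abstract's general sentence indicates that VAS and EQ-5D-5L are measured before surgery. The schedule table is not shown.

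It can also be said that covariates belong in a SAP that is not shown, and that the logistic regression could carry centre. That is fair as to detail. But the article does name its comparison tests, and those tests do not reflect the stated randomisation.

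**Conclusion.** The mismatch is real and its size is modest. Allocation is stratified by centre, and none of the named arm comparisons accounts for centre. If centre is prognostic and balance within centre is achieved, the unstratified primary test is conservative to the extent shown above: slight at SD 0.5, appreciable at SD 1.5. If centres do not differ, nothing is lost by ignoring them. The centre SD and the baseline correlation are assumptions, which is why ranges are given.

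The baseline point is secondary and conditional. It concerns VAS and EQ-5D-5L only, and only if a pre-randomisation value is recorded. Leaving that value out costs precision; it does not make a standard error wrong.

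**What to change.** Before database lock, name one primary analysis that accounts for centre. The preferred form is logistic regression of symptomatic seroma on arm with a random centre intercept, reporting the odds ratio and 95% CI. Do not use fixed centre dummies: with 13-27 centres of 5-10 patients they would be unstable. State that this odds ratio is conditional on centre.

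Add CMH stratified by centre as a sensitivity analysis, and record its downside: with very small centres and 10% loss, it gives up about 1-3.5 power points if centres do not differ.

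State whether VAS and EQ-5D-5L are recorded before randomisation, so that the abstract and the eCRF visit list agree. Where they are, compare arms with a linear mixed model over visits containing baseline value, arm, visit, arm-by-visit and centre, in place of two-sample tests.

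The cost is analysis wording, with no change to recruitment or care. The random-intercept model was not simulated here. With about 60 × 0.25 + 60 × 0.07 ≈ 19 expected events, its behaviour at this size should be checked, and a fallback stated in case it does not converge.

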## Abstract

**Background:**

Seroma after breast cancer surgery is a frequent entity; therefore, different products have been described in literature with the aim to reduce it. The most studied ones have been the sealants products, being tested with aspirative drains. Symptomatic seroma represents the 19% after axillary lymphadenectomy without drains. The aim of this study is to analyze the effect of a sealant in the seroma control after axillary lymphadenectomy without drains and identify the risk factors related to symptomatic seroma.

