### Methods in analysis to handle protocol non-adherence and any statistical methods to handle missing data {20c}

Patients who are included in the study but who do not meet the inclusion or exclusion criteria will be withdrawn from the analysis. Missing data will be excluded for the primary and secondary outcome analyses. Further analyses based on multiple imputation methods will be considered if appropriate. Analyses will be carried out based on the intention to treat principle.

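### The risk-factor model may admit variables because they are significant in univariate tests, and about 19 expected events make that route unreliable

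*Protocol article*

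**What the plan says.** - **Aim.** The abstract of the protocol article gives two aims, the second being to "identify the risk factors related to symptomatic seroma". The same aim appears among the secondary objectives {7}.
- **Entry rule.** Section {20a} assigns the risk-factor analysis to logistic regression. It describes one route of entry as "introducing in the statistical model those variables that show statistical significance in the univariate analysis". A second route, joined to the first in the same sentence, is worded "and/or those that in the bibliography and theoretical framework are prognostic factors". The significance level in the same section is p<0.05.
- **Size.** Section {14} sizes the trial only for the primary comparison. It gives the error rates as "Accepting an alpha risk of 0.05 and a beta risk of 0.2 in a bilateral contrast" and concludes from them that "67 subjects in each study arm are required" for a symptomatic seroma rate "which is expected to be 25% for the control group and 7% for the study group". It adds that "A loss to follow-up rate of 10% has been estimated".
- **Missing outcomes.** Section {20c} states that "Missing data will be excluded for the primary and secondary outcome analyses", so losses reduce the number of events available.

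**The concern.** Choosing covariates by their univariate p-values and then estimating their effects in the same patients has two known costs. A real factor of modest size enters only when its estimate happens to be large, so the factors that enter tend to be overestimated. Factors with no effect also enter at the test's error rate, once for every candidate tried. Both costs depend on the number of events, and this trial was sized for one comparison of two proportions, not for a search among covariates.

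At stake is the trial's answer to a stated aim. A published list of risk factors could omit real ones, include chance ones, and attach odds ratios that the selection rule has pushed away from 1.

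**Working it through.** **1. The plan's own sample size.** Inputs from section {14}: 25% vs 7%, two-sided alpha 0.05, power 0.80, 10% loss.

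- Arcsine formula: h = 2·asin(√0.25) − 2·asin(√0.07) = 0.512, and n = 2 × (1.960 + 0.842)² / h² = 59.96, so 60 per arm. Then 60 / 0.90 = 66.7, rounded up to **67**, which matches the plan.
- Unpooled normal formula: 61.2 per arm, and 61.2 / 0.90 = 68.0, close to the plan.
- Pooled formula: 64 per arm, 72 with loss. With continuity correction: 75, or 84 with loss. Neither matches.

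The 67 is therefore best read as already including the loss, which leaves about 60 evaluable patients per arm.

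**2. Expected events.** Events = n per arm × (0.25 + 0.07).

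| Evaluable per arm | Control | Sealant | Total | 95% sampling range |
|---|---|---|---|---|
| 60 (after 10% loss) | 15.0 | 4.2 | **19.2** | about 12-27 |
| 67 (no loss) | 16.75 | 4.69 | **21.4** | about 14-30 |

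If the sealant had no effect and both arms stood at 25%, the total would be 30.0 to 33.5. With both arms at the abstract's 19%, it would be 22.8 to 25.5. The count is small in every case.

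**3. What a p<0.05 screen does with that many events.** The documents do not give the true odds ratios or the prevalence of the factors, so these are assumed: one binary factor, prevalence 30% or 50%, arm rates held at 25% and 7%, 60 per arm, uncorrected chi-square test at 0.05, simulated. The estimate is the univariate odds ratio in the trials where the factor passes.

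| Assumed true odds ratio | Passes the screen | Median estimate when it passes | Ratio to truth |
|---|---|---|---|
| 1.5 | 11-13% | 3.3-3.5 | 2.2-2.3 |
| 2 | about 25% | 3.5-3.7 | 1.8-1.9 |
| 3 | 51-53% | 3.9-4.3 | 1.3-1.4 |
| 4 | about 70-73% | 4.4-4.9 | 1.1-1.2 |

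At a true odds ratio of 2, over 99% of the estimates that pass exceed the truth. Adding 0.5 to each cell lowers the medians somewhat (to about 3.4-3.5 at a true odds ratio of 2) and does not change the pattern. With 67 per arm, the pass rates rise only to 26-30% at an odds ratio of 2 and 56-58% at 3.

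**4. Chance entries.** If m independent null candidates are each tested at 0.05, the chance that at least one passes is 1 − 0.95^m: 23% for m = 5, 30% for m = 7, 34% for m = 8, 40% for m = 10. The value of m is an assumption. Section {20b} names five subgroup variables, and the other study variables include node count and the block, which would make seven. The article does not call either set the risk-factor candidates.

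**The case against.** The strongest reply is that significance is only one of two entry routes. The sentence in {20a} goes on to factors that the literature and theoretical framework treat as prognostic. An established factor can therefore enter whatever its p-value, and it is then neither missed nor inflated by screening. This stands, and it rules out saying that the model is built by screening alone. It does not remove the problem: for any variable not entered on literature grounds, the significance route remains open.

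Four stronger readings are tempting, and the documents do not support them:

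- **Most real factors would be missed and their odds ratios about doubled.** This depends on true effects that the article does not give. Near-doubling fits a true odds ratio of 2. At 3, about half of factors pass and the inflation is 1.3-1.4-fold. At 4, most pass.
- **The tabulated estimates are what the trial would publish.** They are univariate estimates at the screen. The plan would report multivariable ones from the same patients. The selection carries over, but its size in that model was not computed.
- **The treatment odds ratio would depend on which covariates were selected.** Section {20a} describes the chi-square or Fisher test and the odds ratio separately from the risk-factor model, and nothing says the arm effect is read from that model.
- **The missing candidate list or limit on terms is itself an error.** An article commonly leaves that to the full analysis plan. The point here is the entry rule that the article does state.

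**Conclusion.** The point holds for the stated significance route. The expected count of 19.2 events (21.4 without loss) follows directly from the plan's own rates and size. At that count a p<0.05 screen usually misses factors of modest effect (true odds ratio up to about 2.5) and overstates those it keeps. Among 7-8 independent null candidates it also admits at least one in about three trials in ten.

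The event count rests only on the plan's figures. The pass rates and inflation rest on assumed odds ratios, prevalence, independence and number of candidates, and they weaken as the true effects grow. The issue is confined to a secondary objective and leaves the primary comparison of arms untouched. It still deserves correction, because the rule is written down, serves a published aim, and can be replaced by a change of wording.

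**What to change.** In section {20a}, delete the univariate-significance route for the risk-factor model. Name in advance a short list chosen from the literature: treatment arm plus about 3-4 factors already collected (for example age, neoadjuvant treatment and node count, kept continuous where possible). With one parameter per term, that means 4 to 5 parameters on about 19 events, or 19.2 / 4 = 4.8 to 19.2 / 5 = 3.8 events per parameter. Penalised logistic regression, for example Firth's method, is therefore preferable, though it is one option and not a requirement. Report every term with its 95% confidence interval, whether or not it is significant, and label the analysis exploratory.

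The cost is wording only, with no new data. Fewer factors would be examined, and penalised fitting may need software beyond base SPSS 21.

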### Main hypothesis

The use of Glubran 2® after AL in patients with BC can safely reduce the symptomatic seroma percentage.

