### Trial design {8}

This is a multicenter, international, prospective, double-arm randomized clinical trial with a superiority design. Baseline data will be measured prior to randomization. Follow-up data will be collected at 7, 14, and 30 days after randomization. Long follow-up data will be collected at 6 and 12 months. A CONSORT diagram is presented in Fig. 1.

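### The main hypothesis claims a safe reduction in seroma, but the only inferential method stated for safety is difference testing at p < 0.05 in a sample sized for seroma alone, and a non-significant result there cannot support that claim

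*Protocol article*

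**What the plan says.** In the protocol article, the section Main objectives lists two aims: efficacy against symptomatic seroma, and the safety and tolerability of the sealant. The section Main hypothesis joins them: "The use of Glubran 2® after AL in patients with BC can safely reduce the symptomatic seroma percentage". The section Main safety measures names "adverse events and post-surgical complications such as suture failure and surgical wound infection".

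Statistical methods {20a} fixes how these are compared: "The safety analysis will be performed per protocol and will use the same statistical tests mentioned above". The tests meant, for binary events, are given there too: "For the analysis of qualitative variables, the chi square test or Fisher’s test will be used as appropriate". The same section adds "The OR (odds ratio) is considered as a measure of effect calculated by logistic regression" and "The level of significance is set at *p* < 0.05".

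Trial design {8} describes a "double-arm randomized clinical trial with a superiority design". Sample size {14} ties the number of patients to one outcome: "67 subjects in each study arm are required to detect a statistically significant difference in the percentage of patients with symptomatic seroma", with 25% expected in the control group and 7% in the sealant group, two-sided alpha 0.05, beta 0.2 and 10% loss to follow-up.

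No section states a margin, an acceptable excess risk, a confidence limit or any other between-arm condition for calling the sealant safe.

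**The concern.** A difference test can show harm. When it is not significant, it shows only that the data do not rule out equality, and it says nothing about how large an excess they leave open. The hypothesis contains a safety claim, yet the one inferential method attached to safety cannot confirm such a claim. The sample was not chosen with any complication rate in mind, so a non-significant comparison is a likely result even if the sealant does appreciable harm.

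At stake is the wording of the conclusion. If seroma falls and no complication differs significantly, the hypothesis as written invites a statement that the product safely reduces seroma, and the safety part of that statement could rest on low power. The issue does not depend on the per-protocol population named in {20a}. It is the same if every treated patient is analysed.

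**Working it through.** **Inputs from the protocol article**
- Symptomatic seroma 25% v 7%, two-sided alpha 0.05, beta 0.2, 10% loss, 67 per arm: Sample size {14}.
- Chi-square or Fisher, p < 0.05: Statistical methods {20a}.
- Wound infection 5-15% after axillary lymphadenectomy: Background and rationale {6a}.

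**Assumptions**
- The 5-15% range is used as the control-arm infection rate. The protocol gives it as background from published series, not as an expected rate for this trial.
- A doubling is taken as the harm of interest.
- Allocation is 1:1, from the equal numbers per arm.

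**Step 1. Reproduce the plan's own figure.** Arcsine formula: n = 2(z₀.₉₇₅ + z₀.₈₀)² / h², with h = 2·arcsin√0.25 − 2·arcsin√0.07 = 1.0472 − 0.5355 = 0.5117. So n = 2(1.960 + 0.842)² / 0.5117² = 59.96, that is 60 evaluable per arm. With 10% loss, 59.96 / 0.9 = 66.6, that is 67. The stated figure reproduces with the loss already included, so the safety comparison has between about 60 and 67 patients per arm.

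**Step 2. Chance of missing a doubling of wound infection.** Method: exact enumeration over two independent binomials, two-sided test at 0.05. A detection is a rejection with more infections in the sealant arm. The miss rate is 1 minus the summed probability of those tables.

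| Control → sealant | 67 per arm, chi-square (Fisher) | 60 per arm, chi-square (Fisher) |
|---|---|---|
| 5% → 10% | 81% (89%) | 83% (91%) |
| 10% → 20% | 64% (71%) | 67% (75%) |
| 15% → 30% | 45% (52%) | 49% (58%) |

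By the pooled normal approximation, 80% power for the same doublings would need about 435, 199 and 121 per arm.

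**Step 3. What a non-significant result leaves open (67 per arm, Newcombe 95% intervals for sealant minus control).**
- Equal observed rates, 7/67 v 7/67 (10.4% each): difference 0, interval −10.9 to +10.9 points.
- 15/67 v 7/67 (22.4% v 10.4%): chi-square = 3.48, p = 0.062; Fisher p = 0.10. Neither is significant, yet the observed excess is 11.9 points, with interval −0.8 to +24.4 points.
- An event type seen in none of 67 treated patients: exact upper 97.5% bound 1 − 0.025^(1/67) = 5.4%.

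**The case against.** The strongest objection is that the article contains no faulty decision rule. A reader might infer from {20a} that p > 0.05 will be reported as proof of safety, but no sentence says so. That inference is not supported by the document and is not claimed here.

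Nor is safety assessed only by significance tests. Statistical methods {20a} also provides counts, percentages and an odds ratio. Adverse event reporting {22} has the investigator judge each event's severity and relationship to surgery, with review by the sponsor, and an independent data monitoring committee meets every 6 months. This stands, and it limits the point to the inferential method. None of these provisions supplies a between-arm criterion for *safely*: percentages and an odds ratio come with no stated limit, and event-by-event causality review does not compare the arms.

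A reader might also infer that a doubling would usually be missed across the whole background range. That goes too far: at 15% to 30% with chi-square, the miss rate is 45-49%, slightly less than half.

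It is also fair to say that low power for complications is common in trials sized on a primary outcome, that beta 0.2 was set for seroma and not for safety, and that a criterion for safety could sit in an analysis plan that is not shown. The first two are correct. The third does not dispose of the matter, because the article itself names the safety tests and the threshold, and pairs them with a hypothesis those tests cannot confirm. The objective of assessing safety can be met by estimation. The mismatch lies in the word *safely* in the hypothesis.

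**Conclusion.** The point holds in a limited form. The hypothesis includes a safety claim, the only inferential method stated for safety is difference testing at p < 0.05, and the sample was sized solely for seroma. A non-significant result therefore cannot carry the claim. On the assumptions above, a doubling of wound infection is missed in about 81-91% of trials at a control rate of 5%, 64-75% at 10% and 45-58% at 15% (67 per arm with chi-square to 60 per arm with Fisher). Even perfectly equal observed rates of about 10% leave an excess of about 11 points open.

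The size depends on the assumed control rate and on doubling as the harm that matters. A per-protocol set smaller than 60 per arm would raise the miss rates. No background rate is given for suture failure, so no figure is offered for it. This is a cheap improvement to wording and reporting. It does not show that the trial has committed itself to a wrong reading of its safety data.

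**What to change.** In Statistical methods {20a}:
- For wound infection, suture failure and any adverse event, report the risk difference (sealant minus control) with its 95% confidence interval, and base the safety statement on the upper limit.
- For event types that do not occur, report the exact upper bound.
- State that a non-significant difference is not evidence of safety and that the trial is not powered to exclude harm.

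In Main hypothesis, separate the two parts so that efficacy is tested and safety is estimated. For example: the sealant can reduce the percentage of symptomatic seroma, and the excess risk of complications will be reported with its upper 95% limit.

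The cost is a few sentences and a few more intervals, with no extra patients or data. The drawback is a less favourable safety conclusion: that an excess above a given number of points is excluded, in place of the plain word safe.
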